# Safety and effectiveness of using Disposable Ultrasonic shears to coagulate 5–7 mm blood vessels: protocol for a prospective, multicenter, randomized, parallel controlled, non-inferiority clinical trial

**DOI:** 10.1186/s12893-024-02497-x

**Published:** 2024-07-19

**Keywords:** Disposable Ultrasonic shears, Surgical instruments, 5-7 mm blood vessels, Thoracic surgery

## Abstract

**Background:**

The ultrasonic scalpel is widely used during surgery. It is safe and effective to close the pulmonary artery branch vessels of 7 mm or below with an ultrasonic energy device as reported. However, there have been no multicenter randomized clinical trial to assess the safety and effectiveness of using ultrasonic scalpel to coagulate 5–7 mm blood vessels in thoracic surgery.

**Methods:**

This is a prospective, multicenter, randomized, parallel controlled, non-inferiority clinical trial. A total of 144 eligible patients planning to undergo lung or esophageal surgery will be randomly allocated to the experimental group and the control group. The investigational product (Disposable Ultrasonic Shears manufactured by Reach Surgical, Inc.) and the control product (Harmonic Ace + 7, 5 mm Diameter Shears with Advanced Hemostasis) will be used in each group. The primary endpoint is the success rate of coagulating target blood vessels during surgery. Secondary endpoints include postoperative rebleeding, intraoperative bleeding volume, drainage volume, surgical duration, etc. Postoperative follow-up before and after discharge will be performed.

**Discussion:**

This clinical trial aims to evaluate the safety and effectiveness of using the investigational product (Disposable Ultrasonic Shears manufactured by Reach Surgical, Inc.) and that of the control product (Harmonic Ace + 7, 5 mm Diameter Shears with Advanced Hemostasis) to coagulate 5–7 mm blood vessels in thoracic surgery.

**Trial registration:**

ClinicalTrials.gov: NCT06002737. The trial was prospectively registered on 16 August 2023, https://www.clinicaltrials.gov/study/NCT06002737.

## Introduction

### Background

Ultrasonic scalpel is a safe and effective surgical cutting and hemostasis device [1]. In the 1990s, the ultrasonic scalpel was first used in eye surgeries and neurosurgeries mainly for fine separation. With the development of surgeries, the ultrasonic scalpel is more and more widely used [2]. Due to its advantages such as more precise surgery, no eschar and less smoke, the ultrasonic scalpel is introduced into the laparoscopic and thoracic surgeries [3]. With the accumulation of experience in use and the deepening of studies, the scope of application of the ultrasonic scalpel has been gradually expanded to the resection of stomach, intestine, liver, pancreas, spleen, kidneys, lungs, and pelvic viscera. The ultrasonic scalpel can be used to reduce bleeding, improve the efficacy of surgeries, and reduce the incidence of complications [4, 5].

Several study groups have published data comparing different ways of vascular control such as plastic laparoscopic clips (PCs), titanium laparoscopic clips (LCs), electrothermal bipolar vessel sealer (EBVS), ultrasonic coagulating shears (UCS) [6, 7]. As is reported in the literature, it is safe and effective to close the pulmonary artery branch vessels of 7 mm or below with an ultrasonic energy device [8–13].

However, there have been no prospective multicenter randomized clinical trial to assess the safety and effectiveness of using ultrasonic scalpel to coagulate 5–7 mm blood vessels in thoracic surgery.

### Objectives

This study will be conducted to evaluate the safety and effectiveness of using the investigational product (Disposable Ultrasonic Shears manufactured by Reach Surgical, Inc.) and the control product (Harmonic Ace + 7, 5 mm Diameter Shears with Advanced Hemostasis) to coagulate 5–7 mm blood vessels in thoracic surgery.

## Methods

### Trial design

A prospective, multicenter, randomized, parallel controlled, non-inferiority clinical trial design is used for this Study. Figure 1 shows the design of this clinical trial.

### Participants

To evaluate the safety and effectiveness of Disposable Ultrasonic Shears, a total of 144 patients will be recruited from 4 high-volume tertiary hospitals in China. Written informed consent is obtained from each patient.

### Inclusion criteria

The patients participating in this trial must meet all the following criteria:

(1) Ages from 18 to 75 years;

(2) Any planned anatomic lung resection (segmentectomy or lobectomy).

(3) A 5–7 mm blood vessel to undergo coagulation during surgery;

(4) Able to sign the ICF;

(5) Able to understand the trial and cooperate in the procedures.

### Exclusion criteria

The patients meeting any of the following exclusion criteria will be excluded:

(1) Body Mass index (BMI) ≥ 35.0 kg/m2;

(2) Prothrombin Time (PT) > 5 s;

(3) Target blood vessels invaded by tumors;

(4) Variations, malformations or calcifications of the target blood vessels;

(5) Preoperative chemotherapy and/or radiotherapy;

(6) Fasting Plasma Glucose (FPG) ≥ 11.1 mmol/l;

(7) Hypertension with poorly controlled blood pressures;

(8) Pregnant or lactating women;

(9) Participated in any other clinical trial within 3 months;

(10) Mental disorders and unable to act autonomously;

(11) Any other circumstances that the investigators consider inappropriate for enrollment.

### Withdrawal criteria

(1) Withdrawing the ICF;

(2) Inappropriate to continue considered by the investigators;

(3) Damage to the target blood vessels before coagulation;

(4) Dead patients;

(5) Lost to follow-up;

(6) Termination of the clinical trial as required by the Sponsor.

**Fig. 1 Fig1:**
[figure not shown]
Flowchart of trial design

### Interventions

#### Arm A — using experimental disposable ultrasonic shears for coagulation

In the experimental group, the investigational product (Disposable Ultrasonic Shears manufactured by Reach Surgical, Inc.) will be used to coagulate 5–7 mm blood vessels.

#### Arm B — using harmonic ace + 7(Ethicon Endo-Surgery, LL), 5 mm diameter shears with advanced hemostasis for coagulation

In the active control group, the control product (Harmonic Ace + 7, 5 mm Diameter Shears with Advanced Hemostasis) will be used to coagulate 5–7 mm blood vessels.

### Outcomes

#### Primary endpoint

The primary endpoint is the success rate of coagulating target blood vessels during surgery. Successful coagulation is defined as follows:

After the coagulation with Disposable Ultrasonic Shears, if there is no bleeding before the chest or abdomen is closed, the coagulation is regarded as a success. If the coagulated blood vessel rebleeds and needs to be treated with other hemostatic methods such as stapler, vascular clamp or suturing, the coagulation is regarded as a failure.

#### Secondary endpoint

The secondary endpoint measures will be: (1) Postoperative rebleeding, (2) Intraoperative bleeding volume, (3) Drainage volume, (4) Surgical duration, (5) Operation performance evaluation of the medical device, (6) Stability of the complete machine.

#### Safety endpoints

The safety endpoint will be: (1) Frequency of AEs and SAEs, (2) Frequency of medical device-related AEs and SAEs, (3) Frequency of device defects.

### Collection of general data

The general data of patients will be collected: (1) Demographic data: gender, date of birth, height, weight and others, (2) Laboratory tests: Routine blood test, Blood biochemical test, Coagulation function test, Glucose, etc.

### Sample size calculation

A study was conducted to evaluate the effectiveness of an ultrasonic vascular closure device for closure of pulmonary artery branches of 7 mm or below during the minimally invasive anatomic lung resection [10]. The immediate success rate reported in the Liberman study was 98.7%. In combination with literature reports and clinical conditions, assuming a success rate of 96% for coagulation of target blood vessels during surgery with an ultrasonic scalpel in the experimental group and control group, a non-inferiority margin of 10.00%, a significance level of 0.025 (single-sided), and a power of 80%, the calculated sample size is 61 cases for the test group and the control group respectively when subjects are assigned to the experimental group and the control group at a ratio of 1:1. Considering a drop-out rate of about 15%, the sample size for each group is 72 subjects, totally 144 subjects.

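### At the assumed 96% success rate, 61 per group does not give 80% power at one-sided 2.5%: a test that holds its level has about 65%

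*Protocol article*

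**What the plan says.** The Sample size calculation section of the protocol article gives every input. It plans on equal rates: "assuming a success rate of 96% for coagulation of target blood vessels during surgery with an ultrasonic scalpel in the experimental group and control group". It then states "a non-inferiority margin of 10.00%, a significance level of 0.025 (single-sided), and a power of 80%, the calculated sample size is 61 cases" per group with 1:1 allocation, and continues: "Considering a drop-out rate of about 15%, the sample size for each group is 72 subjects, totally 144 subjects". The same section cites a published immediate success rate of 98.7% for ultrasonic closure of pulmonary artery branches.

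The article names neither the sample size formula nor the test or interval for the primary comparison. The Effectiveness evaluation section says only that the primary endpoint is assessed in the FAS and the PPS.

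**The concern.** The sample size matches a formula that takes its variance at 96% in both groups. At the non-inferiority boundary the experimental success rate is 10 points below control, and the variance there is much larger. With so few expected failures, the normal approximation to the difference is also poor. The stated pair of one-sided 2.5% error and 80% power may therefore not belong to this design.

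Two things are at stake. If the analysis uses the Wald interval, a device that is truly 10 points worse is declared non-inferior about twice as often as stated. If it uses an interval that holds its level, the trial misses non-inferiority between identical devices about one time in three with 61 evaluable per group. The protocol states one in five.

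**Working it through.** **Inputs (Sample size calculation section).** Success 96% in both groups; margin 10 points; one-sided alpha 0.025; power 80%; 1:1 allocation; 61 evaluable per group; 15% drop-out; 72 per group.

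**1. Reproducing the plan's figures.** Unpooled normal approximation:

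n = (1.960 + 0.842)² × 2 × 0.96 × 0.04 / 0.10² = 7.849 × 0.0768 / 0.01 = 60.28, rounded up to 61.

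Drop-out: 61 / 0.85 = 71.8, rounded up to 72. Both figures reproduce, so there is no slip in the calculation.

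**2. Why the approximation is weak here.** Expected failures per group are 61 × 0.04 = 2.4. The per-subject variance sum in the formula is 2 × 0.96 × 0.04 = 0.0768. On the boundary at 86% versus 96% it is 0.86 × 0.14 + 0.96 × 0.04 = 0.1588. At the restricted estimates used by the score test (87.7% and 97.7%) it is 0.1301.

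**3. Exact operating characteristics.** For each rule, the binomial probabilities were summed over all tables in which the lower limit of the two-sided 95% interval lies above −10 points (for the score tests, those in which the one-sided 2.5% test rejects). Power is taken at 96% in both groups. Error is taken where the experimental rate is exactly 10 points below control.

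| Rule | n per group | Power at 96%/96% | Error at 86%/96% | Error at 88.7%/98.7% | Maximum error, all control rates |
|---|---|---|---|---|---|
| Wald | 61 | 81.9% | 4.5% | 5.7% | 5.8% |
| Farrington–Manning, Miettinen–Nurminen | 61 | 64.6% | 1.9% | 1.9% | 2.7% |
| Newcombe | 61 | 66.3% | 2.5% | 2.0% | 2.7% |
| Wald | 72 | 83.8% | 3.4% | 4.4% | 6.2% |
| Farrington–Manning, Miettinen–Nurminen | 72 | 73.5% | 2.3% | 1.8% | 2.6% |
| Newcombe | 72 | 73.5% | 2.3% | 1.8% | 2.7% |

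The 2.7% maxima for the score and Newcombe rules occur at control rates far from 96%. For control rates of 90% or more at n = 61, the score rule stays at or below 2.3%, and Newcombe reaches 2.6%.

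**4. Could another test rescue the claim?** A linear program maximised power at 96%/96% over all monotone tests with error at or below 2.5% on a grid of boundary points. At 61 per group the maximum is 68.8%.

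**5. What 80% would need at 96%.** Farrington–Manning formula:

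n = [(1.960 × √0.1301 + 0.842 × √0.0768) / 0.10]² = 88.4, rounded up to 89.

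Exact score power first touches 80% at 81 per group, dips to 79.6% at 83, and stays at or above 80% from 84.

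**6. Sensitivity to the true success rate (score test, same rate in both groups).**

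| True success rate | n = 61 | n = 72 |
|---|---|---|
| 95% | 58% | 68% |
| 96% | 65% | 74% |
| 97% | 73% | 80% |
| 98% | 82% | 88% |
| 98.7% (cited rate) | 89% | 95% |

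**The case against.** Four points can be made for the plan.

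- **The arithmetic is right, and planning with a normal approximation is conventional.** This is true. What fails is the claim about error and power attached to the result, not the calculation of 61 or 72.
- **The article commits to no test, and the SAP may name one.** The inflated error of 4.5% to 5.8% does depend on a Wald analysis, and that part of the concern is conditional. The power part is not: at 61 per group, no monotone test that holds 2.5% gets above about 69%.
- **61 is the worst case.** Coagulation success is judged before the chest or abdomen is closed and recorded on the day of surgery, so later loss to follow-up cannot remove it. Some earlier loss remains possible, such as damage to the vessel before coagulation or withdrawal of consent. The FAS could therefore be close to 72 per group. This softens the shortfall, but power at 72 is still 74%, about one miss in four. The Wald error at the design rates falls to 3.4% but still exceeds the stated 2.5%.
- **96% is cautious next to the cited 98.7%.** If the cited rate holds in both groups, power is ample. That is worth stating, but the protocol makes its 80% claim at 96%.

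The score and Newcombe intervals hold 2.5% only approximately. The excess is at most about 0.2 points, and strictly exact unconditional tests had lower power still (56% to 64% at 61 per group).

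**Conclusion.** The concern holds. Under the protocol's own assumptions (96% in both groups, 10-point margin, one-sided 2.5%, 61 evaluable per group), 80% power and 2.5% error cannot both be had. With an interval that approximately holds its level, power is about 65% at 61 per group and 74% at 72. With the Wald interval, power is about 82% at 61 per group, but the true one-sided error is 4.5% at the design boundary and up to 5.8% when control success is close to 100%. That inflation applies to control rates of about 96% and above; at a 90% control rate the Wald error is 2.9%.

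The power shortfall depends on the 96% planning value and shrinks quickly as the true rate rises: the score test reaches 80% at a true rate of 97% with 72 per group, and 89% at 98.7% with 61. The stated power is wrong as written and should be corrected before analysis.

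**What to change.** Keep 144 patients and make two changes of wording.

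1. In the primary analysis, name the Miettinen–Nurminen (or Newcombe) two-sided 95% interval for the difference in success rates, with non-inferiority declared if its lower limit lies above −10 points. If the SAP already names such an interval, cite it.
2. In the sample size section, replace the 80% by exact figures: at 96% success, about 65% power with 61 evaluable per group and about 74% with all 72; at the cited 98.7%, about 89% and 95%.

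The cost is a less favourable power statement, with no added patients. If the sponsor would rather keep 80% power at 96%, the design needs about 84 (exact) to 89 (formula) evaluable per group. With 15% drop-out that is 84/0.85 = 98.8, so 99, to 89/0.85 = 104.7, so 105 per group, or 198 to 210 in total.

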### Allocation

This Study will be simultaneously carried out at multiple clinical centers, and the number of subjects included at each center will be distributed as evenly as possible. In view of the feasibility and inclusion progress, however, the number of subjects enrolled at each participating center will be adjusted according to the actual conditions to ensure the balance of the size included at each center, and for a specific center, the final size enrolled should not be greater than 50% of the total number of subjects.

### Assessment and follow-up

**Visit 1: screening period (Day-14 to Day 0)**.

The visit include:

(1) Patients voluntarily sign the ICF;

(2) Demographic data of the subjects: gender, date of birth, height, weight and others;

(3) Vital signs: heart rate and blood pressure;

(4) Review of inclusion and exclusion criteria;

(5) Current/previous medical history;

(6) Laboratory tests and CT examination.

**Visit 2: surgical period (the day of surgery**,** Day 0)**.

(1) Intraoperative blood vessel diameter measurement;

(2) Whether it is successful to coagulate the target blood vessel;

(3) Type of the coagulated blood vessel, surgical duration and intraoperative bleeding volume;

(4) Surgery name and the specification, model and quantity of investigational products;

(5) Operation performance of the medical device;

(6) AEs and concomitant medications;

(7) Stability of the complete machine and the device defects.

**Visit 3: postoperative follow-up before discharge (after surgery and before discharge)**.

(1) Occurrence of post-operative rebleeding;

(2) Drainage volume;

(3) AEs and concomitant medications.

**Visit 4: follow-up 30 days (30 ± 7 days) after surgery**.

(1) Occurrence of post-operative rebleeding;

(2) AEs and concomitant medications;

### Adverse events

Adverse event (AE) refers to any adverse medical events occurring to the subjects regardless of their relevance to the investigational medical device.

The investigators should identify the presence of AEs and their occurring dates, severities, treatments and prognoses, and relevance to study-related medical devices, operations or drugs when the subjects recruited in the clinical study are evaluated at each visit.

### Data management

The data collection/management system of this project is the electronic data collection (EDC) system. The EDC system that has been systematically verified and designed with trace management and user permission management functions will be selected. To protect confidentiality, only authorized and trained investigators will have access to the data of enrolled patients.

### Statistical methods

#### General rules

(1) Statistical description.

The mean, standard deviation, median, minimum, maximum, lower quartile (Q1) and upper quartile (Q3) will be calculated in the description of quantitative indicators. Grade indicators will be used to describe the cases and percentage of each grade.

(2) Statistical inference.

The general conditions of two groups will be compared. The data distribution-based group t-test or Wilcoxon rank sum test will be used for the intergroup comparison of quantitative indicators. Chi-square test or Fisher’s exact test (if the Chi-square test is not applicable) will be used for the categorical data. Wilcoxon rank sum test or CMH test will be used for ranked data.

All statistical tests should be two-sided tests unless otherwise specified, and the tested difference will be regarded to be statistically significant in case of a P value of below 0.05 (two-sided). In addition to the statistical methods listed below, detailed and additional exploratory analyses may be required and confirmed in the clinical study report and statistical analysis plan (SAP).

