#### Effectiveness evaluation

(1) Primary endpoint:

The primary endpoint is the success rate of coagulating target blood vessels during surgery, which will be evaluated based on the FAS and PPS.

(2) Secondary endpoints:

The secondary effectiveness evaluation is based on the FAS and PPS. Suitable descriptive indicators and hypothesis test methods will be selected for the statistical description and inference of data according to the characteristics of such data.

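### Bleeding volume, drainage volume and surgical duration would probably be estimated more precisely with one pre-specified model adjusted for centre and planned procedure than with an unadjusted test chosen from the data

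*Protocol article*

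**What the plan says.** Under General rules, the protocol article gives one rule for all quantitative outcomes: "The data distribution-based group t-test or Wilcoxon rank sum test will be used for the intergroup comparison of quantitative indicators". It names no covariate or stratum and no criterion for choosing between the two tests. Under Effectiveness evaluation, the secondary endpoints are again left to the data: "Suitable descriptive indicators and hypothesis test methods will be selected for the statistical description and inference of data according to the characteristics of such data". General rules adds that further detailed and exploratory analyses may be settled in the clinical study report and the SAP. The SAP is not shown.

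The Secondary endpoint section lists three outcomes that are clearly quantitative: intraoperative bleeding volume, drainage volume and surgical duration.

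On the structure of the trial, Participants says that "a total of 144 patients will be recruited from 4 high-volume tertiary hospitals in China". Allocation aims for even recruitment but allows adjustment, and for any one centre "the final size enrolled should not be greater than 50% of the total number of subjects". The Inclusion criteria admit planned segmentectomy or lobectomy. The abstract is broader: "A total of 144 eligible patients planning to undergo lung or esophageal surgery". The definition of the primary endpoint also refers to closing the chest or the abdomen. The article does not say whether randomisation is stratified by centre or procedure.

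**The concern.** Centre and planned procedure are known before the operation, and both can plausibly affect how long it takes, how much the patient bleeds and how much drains afterwards. An unadjusted two-group test leaves that variation in the error term. If the arms differ by chance in their mix of centres or procedures, the difference also enters the estimate.

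The choice between tests has a further effect. The t-test compares means and the Wilcoxon test compares ranks. Until someone has looked at the distribution, the reader does not know which contrast each endpoint will report.

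What is at stake is the precision and clarity of three secondary comparisons in a trial sized for a different, binary outcome.

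**Working it through.** **The plan's own figure.** Sample size calculation assumes 96% success in both arms, a 10-point margin, one-sided 0.025 and 80% power. With unpooled variance:

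(1.960 + 0.842)² × 2 × 0.96 × 0.04 / 0.10² = 60.3, so 61 per arm; 61 / 0.85 = 71.8, so 72 per arm and 144 in total.

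The stated figure reproduces. It rests on the primary endpoint and does not depend on how the secondary endpoints are tested.

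**Inputs for the precision check.** N is 144, or 122 (2 × 61) after the planned drop-out. Four centres need 3 terms and two procedure categories need 1, so q = 4. All 8 centre-by-procedure strata need q = 7. R² is the share of outcome variance explained by these factors. It is an assumption, taken from 0 to 0.30, because the article gives no standard deviation, centre effect or procedure effect.

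**Formula.** Variance ratio, adjusted to unadjusted = (1 − R²) × (N − 3) / (N − 3 − q). The interval-width ratio is its square root. Example at R² = 0.10, N = 144, q = 4: 0.90 × 141/137 = 0.926, and the square root is 0.962.

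Power is shown for the difference that the unadjusted test detects with 80% power at 72 per arm: 2.802 × √(2/72) = 0.467 SD.

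| R² | Width ratio, q = 4 | Power, q = 4 | Width ratio, q = 7 | Power, q = 7 |
|---|---|---|---|---|
| 0 | 1.014 | 78.9% | 1.026 | 78.0% |
| 0.05 | 0.989 | 80.9% | 1.000 | 80.0% |
| 0.10 | 0.962 | 82.9% | 0.973 | 82.1% |
| 0.20 | 0.907 | 87.0% | 0.917 | 86.3% |
| 0.30 | 0.849 | 91.0% | 0.858 | 90.4% |

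At N = 122 and R² = 0 the width ratios are 1.017 (q = 4) and 1.031 (q = 7).

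**Break-even.** Setting the variance ratio to 1 gives R² = q / (N − 3). At N = 144 this is 4/141 = 0.028 or 7/141 = 0.050.

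**Is the stated rule valid?** The rule was simulated at 72 per arm, with 3000 trials per scenario and normal and log-normal outcomes. A Shapiro-Wilk test stood in for the unspecified criterion.

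- With simple randomisation, type I error of the chosen test was 0.048 to 0.056. The Monte Carlo standard error is √(0.05 × 0.95 / 3000) = 0.004, so this is compatible with 0.05.
- With randomisation blocked by centre and R² = 0.30, the chosen test was conservative (0.032 to 0.036). The adjusted model stayed near nominal (0.050 to 0.055).
- Power at 0.467 SD, chosen test against adjusted model (on the log scale for log-normal data):
  - normal: 80% against 79% at R² = 0, 79% against 82% at 0.10, 80% against 91% at 0.30;
  - log-normal: 78% against 79%, 77% against 82%, 77% against 90%.

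**The case against.** The strongest reply is that this belongs to the SAP. A condensed article may name default tests and leave covariates, transformations and the normality criterion to the fuller document, which may already contain an adjusted model. The quoted sentence also directly follows one on comparing the general conditions of the groups. This has weight, and it is why the point is not an omission. But the article does state a rule for quantitative outcomes in general, and its section on secondary endpoints repeats the principle of choosing by the data. If the SAP already adjusts, the wording only needs to be aligned.

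Four stronger readings are tempting and are not supported.

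- A reader might infer that choosing the test from the data inflates type I error. The simulation shows no inflation; at worst the rule is conservative.
- A reader might infer that adjustment is free. It is not: with factors that predict nothing, intervals widen by 1.4% to 3.1%.
- A reader might use √(1 − R²) alone, which gives 0.949 at R² = 0.10 and 0.837 at 0.30, or 11% to 43% more patients. That ignores the lost degrees of freedom. The net figures with q = 4 are 1/0.926 − 1 = 8% and 1/0.720 − 1 = 39%, and both rest on an assumed R².
- A reader might infer that one large centre biases the comparison. Unequal centre sizes alone do not bias a randomised comparison. Only a chance imbalance between arms within centres matters, and 50% is a ceiling, not a forecast.

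Two practical objections also stand. The visit schedule lists the surgery name on the day of operation and no separate item for planned procedure at screening. A van Elteren test does not by itself give an adjusted difference with an interval.

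**Conclusion.** This is an inexpensive improvement to three secondary endpoints, not an error. The stated rule is valid, but it is less precise than an adjusted analysis if centre and planned procedure explain more than about 3% to 5% of the variance, and it leaves the effect measure open until the data are seen. With four terms and 144 patients, the change in interval width runs from +1.4% at R² = 0 to −15% at R² = 0.30. The worst case considered, 122 patients and eight strata with no prognostic value, is about 3% wider. An R² above break-even is plausible for these outcomes, but the article gives no figure to confirm it. The primary non-inferiority conclusion and the sample size do not change.

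**What to change.** Name one method per quantitative secondary endpoint before the data are examined:

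- **Model:** a linear model with treatment, centre and planned procedure.
- **Scale:** bleeding and drainage volume on the log scale, fixed outright and not made conditional on observed skewness, with a rule for zero values set in advance. Surgical duration untransformed.
- **Report:** the adjusted difference for duration and the adjusted ratio for the volumes, each with its 95% interval.
- **Supportive analysis:** a van Elteren test stratified by centre.
- **Remove:** the choice between t-test and Wilcoxon test for these endpoints.

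First reconcile the abstract, the inclusion criteria and the primary endpoint definition on whether esophageal surgery is eligible, and define the procedure categories only then. Define them by the planned procedure, recorded before randomisation, and not by the operation performed. If that cannot be recorded, or recovered for patients already enrolled, adjust for centre only. This uses 3 terms and widens intervals by at most √(141/138) − 1 = 1.1% at N = 144.

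The cost is a change of wording in the protocol and SAP, possibly one additional data field, and a few degrees of freedom.
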